### Interventions

All qualified participants will be randomly assigned to one of two groups: the integrative medicine group or the standard care group. Standard care—comprising basic treatment, general nursing care—and exercise therapy will be provided to both groups. The integrative medicine group will also receive acupuncture, Chinese herbs, and rTMS. Participants will receive acupuncture and rTMS treatments five times per week for 4 weeks and receive Chinese herbs, basic treatment, general nursing care, and exercise therapy for 4 weeks. All treatments will be carried out by expert acupuncturists and rehabilitation therapists, who will follow standard operating protocols to ensure that each patient receives the same treatments.

The intervention is described following the Template for Intervention Description and Replication (TIDieR) checklist:

#### Integrative medicine group

In addition to standard care that is the same as the control group, the integrative medicine group will receive acupuncture, Chinese herbs, and rTMS.

(1) Acupuncture:

The acupuncture method of the trial will comprise a combination of scalp acupuncture (SAC NTCoAaMo, 2021) and body acupuncture.

Scalp acupuncture includes the middle line of the forehead (MS1), the front line by the forehead (MS2), and the middle line of the vertex (MS5). These acupoints are needled for 1 inch with the direction of the scalp tilted 15–30 degrees. The scalp needles are kept for 1 h, with two times the intermittent manipulation of the needle, 10 s, 200 r/min. The treatment frequency is one time per day and five times per week across 4 weeks.

Body acupuncture points include Yintang (GV29), Taichong (LR3), Shenmen (HT7), Neiguan (PC6), Danzhong (CV17), Qimen (LR14), and Taixi (KI3). After local disinfection, the Yintang (GV29) acupoint is needled for 0.3–0.5 inches with the horizontal insertion of the needle direction. The bilateral Taichong (LR3) acupoints are needled for 0.5–0.8 inches in the straight direction. The Danzhong (CV17) and bilateral Shenmen (HT7) acupoints are needled for 0.3–0.5 inches in the straight direction. The bilateral Neiguan (PC6) and Taixi (KI3) acupoints are needled for 0.5–1 inch in the straight direction. The bilateral Qimen (LR14) acupoint is needled for 0.5–0.8 inches with the horizontal insertion of needle direction. The body needles are kept for 30 min; the treatment frequency is five times per week, and the treatment duration is 4 weeks.

(2) Chinese herbs

The Chinese herbs called “Chaihushugan powder” include the following prescriptions (Yu and Fang, 2018): Chaihu 12 g, Chenpi 12 g, Chuanxiong 9 g, vinegar Xiangfu 9 g, Zhike 9 g, Shaoyao 9 g, and roasted Gancao 3 g.

The dosage is to take the granules with 100 ml of warm water two times a day (after breakfast and dinner) for 4 weeks.

(3) rTMS

rTMS equipment: CCY-I-type magnetic field stimulator

rTMS protocol: The stimulus is applied over the left dorsolateral prefrontal cortex (DLPFC) and the left temporal lobe. The stimulation parameters are as follows: 100% magnetic field strength relative to the patient's observed resting motor threshold, at 10 pulses per s for 5 s, with an intertrain interval of 50 s. One treatment session lasts 30 min (30 trains) and comprises 1,500 pulses. The frequency and treatment course of rTMS is five times per week for 4 weeks.

#### Standard care group

(1) Basic pharmacological treatment

The specific methods of the basic pharmacological treatment are formulated concerning the *Guidelines for prevention and treatment of cerebrovascular diseases in China (2010 Edition)*. When appropriate, corresponding drugs that have the effect of lipid regulation, blood sugar control, antihypertension, and anticoagulation will be used depending on the patient's primary diseases and complications. The antidepressant drug is paroxetine tablets (Beijing Fuyuan Pharmaceutical Co., Ltd., Guoyao Zhunzi: h20133084) 20 mg, taken orally after meals every morning.

(2) General nursing care

The nursing staff will assess the general condition, psychological status, and family status of the patients. They will also strengthen guardianship, communicate with the patients, reduce insecurity of the patients, and prevent unsafe incidents such as suicide. Nursing care will be provided to keep the patients' sleep, diet, and environment comfortable.

(3) Exercise therapy

A professional therapist will assess the patient's Brunnstrom stage. In accordance with the impairment of the patient's motor functions (e.g., muscle tone, muscle strength, balance, movement coordination, and proprioception), an individualized scheme of exercise therapy will be developed. The scheme of exercise therapy includes proper limb positioning, joint range-of-motion training, muscle strength training, turnover, transfer training, sitting, standing balance training, gait training, and so on. One session will last for 30–45 min. The treatment frequency and treatment course of exercise therapy will be once a day for 4 weeks (Yu and Park, 2013; Bang and Son, 2016).

Standard care (including basic pharmacological treatment, general nursing care, and exercise therapy) is a fundamental treatment for stroke and PSD. It is worth noting that after receiving 4 weeks of the aforementioned standard care in both the integrative medicine and standard care groups, specialist physicians will determine whether such standard care approaches should be continued based on the individual recovery conditions.

### Outcome measures

#### Primary outcomes

The primary outcome will be measured at baseline, week 4 after treatment, and week 8 during follow-up.

##### Hamilton depression scale

The HAMD, originally published by Max Hamilton (Hamilton, 1960), is a standard efficacy outcome in antidepressant clinical trials (Chagas et al., 2010). The participants will be rated on 17 dimensions on a 2- or 4-point scale. The higher the score, the more serious the condition of depression. A score of 0–7 is considered to have depressive symptoms, a score of 8–17 is considered to be possible depression, a score of 18–24 is considered to be clear depression, and a score of 25–52 is considered to be severe depression. It takes ~20 m to complete the assessment.

##### Self-rating depression scale

The self-rating depression scale was developed by W.K. Zung in 1965. It can reflect the depressive state and its variability well (Zung, 1965). The scale contains 20 items scored on a 4-point scale. The rough scores were obtained by summing each of the 20 new items, multiplying the rough scores by 1.25, and then taking the integer part as the standard score. A standard score of 50–59 is considered to be a mild depressive mood, a standard score of 60–69 is considered to be moderate depression, and a standard score of more than 70 is considered to be severe depression. Patients respond according to their situation in the past week.

##### Activity of daily living scale

The ADL was developed in 1969 by Lawton and Brody in the U.S. (Lawton and Brody, 1969). The scale has two parts: the Physical Self-Maintenance Scale and the Instrumental Activities of Daily Living Scale. It is principally used to assess the subject's ability to perform daily living activities. The range of scores is from 20 to 80, with higher scores indicating more functional impairment (Liu et al., 2018). A score of more than 23 is considered a cognitive impairment.

#### Secondary outcomes

The secondary outcome will be measured at baseline, week 4 after treatment, and week 8 during follow-up.

##### Montreal cognitive assessment scale

The MoCA was developed based on clinical experience and concerning the Mini-Mental State Examination. It is a common way to assess a tester's awareness and is more sensitive to detecting mild cognitive impairment. Not only that, but the MoCA and its subtests are reliable and valid for assessing global and specific cognitive performance in patients with depression, and it could be a tool for screening neurocognitive deficits in depressed patients (Srisurapanont et al., 2017). The scale covers eight cognitive domains, including attention and concentration, executive function, memory, language skills, visual structure, abstract thinking, numeracy, and orientation, among other 11 items. The total score is 30 points. Add 1 point if the number of years of education is ≤12 years, and a score of ≥26 is considered normal.

##### The Fugl-Meyer assessment scale

The FMA scale is one of the most extensively used and recognized methods for assessing motor function (Rech et al., 2020), with a score of 100 for motor function (66 for upper extremity motor function and 34 for lower extremity motor function). The higher the score, the better the motor function.

##### Pittsburgh sleep quality index

The PSQI was developed in 1989 by Buysse et al. (1989), a psychiatrist at the University of Pittsburgh, to assess the quality of sleep of subjects in the last month. This scale can be used not only to assess sleep behavior and habits in the general population but also has a high level of reliability and validity (Mollayeva et al., 2016). It can be used for the general evaluation of sleep quality in clinical patients. A score of 0–5 is considered to be good sleep quality, a score of 6–10 is considered to be OK sleep quality, a score of 11–15 is considered to be average sleep quality, and a score of 16–21 is considered to be very poor sleep quality.

### Safety assessment

To avoid AEs, such as local bleeding or discomfort at the acupuncture points, local redness or bruising, itching, and dizziness, the participants' safety will be monitored throughout the treatment. The timing of onset, intensity, progression, and management of the AEs will be meticulously noted at each visit. If a major adverse event occurs, the primary investigator and the institutional review board will be notified as soon as possible, and immediate action will be taken.

### Data collection and management

In this study, case report form (CRF) tables will be used to collect data. The assessment of the HAMD and SDS scales will be completed by psychiatrists, and trained physicians will complete the other scales through conversations and physical examination. Among them, the scale assessment for the follow-up period will be performed by telephone follow-up. The data manager is specifically trained in transcribing the data from CRFs to the database used for the statistical analyses.

### Statistical analysis

Statistical analyses will be carried out by statisticians unaware of the groupings. The statistical analysis will be performed using SPSS software version 25.0. A two-sided 5% significance level will be adopted, and the corresponding 95% CI will be calculated to the greatest extent possible. A *p*-value of <0.05 will be set as the significance level.

Demographic characteristics and baseline measurements of the variables in each group will be summarized. Measurement data that conform to a normal distribution will be displayed using the mean ± SD, while the median, minimum, and maximum will describe measurement data that do not conform to a normal distribution. To assess the treatment effectiveness, outcome measurement data at baseline, after the intervention, and follow-up (i.e., 4 and 8 weeks), will be analyzed. For the qualitative data, the difference between and within groups will be tested by the chi-square or Fisher's exact test. For quantitative data, either parametric tests (Student's *t*-test) or non-parametric tests (Mann–Whitney *U*-test, Wilcoxon signed-rank test) will be used, depending on the normality of the distribution. In addition, the intention-to-treat analysis will be carried out to minimize potential attrition bias.

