### Sample size calculation

The data statistician will carefully compute the appropriate sample size for each group based on the difference in postintervention HAMD scores between the two groups. According to our unpublished pilot study, the HAMD score (mean ± standard deviation) in the standard care group was 16.5 ± 4.51, and the HAMD score in the integrative medicine group was 14.5 ± 3.40. The mean HAMD score in the integrative medicine group was 2 points lower than that in the standard care group. Based on a 5% false-positive error rate (α = 0.05, two-sided, the normal distribution quantile table shows that *Z*_1−α/2_ = 1.96) and 90% power (β = 0.1, the normal distribution quantile table shows that *Z*_1−β_ = 1.28), the sample size is estimated as follows:

$$\begin{array}{l} \begin{array}{l} n=\frac{{\left(Z_{1-\alpha /2}+Z_{1-\beta }\right)}^{2}\times (\sigma_{1}^{2}+\sigma_{2}^{2})}{\delta^{2}}\\ \;=\frac{{\left(1.96+1.28\right)}^{2}\times (3.40^{2}+4.51^{2})}{2^{2}}\approx 83.72 \end{array} \end{array}$$

Each group needs to include 84 participants. Assuming an ~20% dropout rate, a total of 202 participants will be enrolled in this trial.

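### Chi-square and Fisher's exact tests are prescribed for within-group categorical change, where the same patients are compared with themselves; within-group tests are also not marked as secondary to the randomised comparison

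*Protocol article*

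**What the plan says.** The Statistical analysis section sets the purpose and the visits in one sentence: "To assess the treatment effectiveness, outcome measurement data at baseline, after the intervention, and follow-up (i.e., 4 and 8 weeks), will be analyzed". It then gives one rule for categorical data: "For the qualitative data, the difference between and within groups will be tested by the chi-square or Fisher's exact test". No paired categorical test is named. For quantitative data it lists Student's t-test, without saying whether paired or independent, the Mann–Whitney U-test and the "Wilcoxon signed-rank test". The last of these is a paired method, so before-after testing is planned. On the error rate: "A two-sided 5% significance level will be adopted".

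The Integrative medicine group section describes the add-ons as given "In addition to standard care that is the same as the control group". The Standard care group section lists nursing care and exercise therapy and names the drug: "The antidepressant drug is paroxetine tablets". Both arms therefore receive the antidepressant, the nursing and the exercise therapy.

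The Outcome measures section defines three primary and three secondary outcomes, all as scale scores. Severity bands are given for HAMD, SDS and PSQI, but only as descriptions of the scales.

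**The concern.** Pearson's chi-square test and Fisher's exact test both compare independent samples. A within-group comparison of a category at baseline and at week 4 has one sample measured twice. Its variance depends on how strongly a patient's two results agree, and neither test uses that information. The p-value is therefore wrong even when the table is filled in correctly. A test is named for the paired case and it is the wrong one, so this is not a detail left for later.

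There is a second, weaker point. Within-group tests appear under the heading of treatment effectiveness with the same standing as the between-group tests. In this design a fall in HAMD within the integrative arm mixes the add-ons with paroxetine, nursing, exercise therapy and natural recovery. A reader of the results could take a small within-arm p-value as evidence for the package when only the randomised comparison can supply it.

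**Working it through.** **1. The plan's own figure.** The Sample size calculation section uses HAMD "in the standard care group was 16.5 ± 4.51" and "the HAMD score in the integrative medicine group was 14.5 ± 3.40". The formula is n = (1.96 + 1.28)² × (3.40² + 4.51²) / 2² = 10.4976 × 31.9001 / 4 = 83.72, so 84 per group. This reproduces the stated value. It rests on the between-group difference after treatment; the article states no figure for any within-group test.

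**2. Inputs for the check.** From the article: two-sided α of 0.05, 101 per arm, about 20% dropout, hence 101 × 0.8 = 80.8, taken as 81 per arm. Assumed, because the article does not give them: the proportion in a category at each visit and the within-patient correlation.

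**3. Actual size of chi-square on paired data.** When the proportion is the same at both visits, the true variance of the difference is 2p(1 − p)(1 − φ)/n, where φ is the correlation of the two binary results. Chi-square uses about 2p(1 − p)/n. The actual size is therefore about 2 × [1 − Φ(1.96/√(1 − φ))].

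With proportion 0.5 at both visits and latent normal correlation 0.5:
- φ = (2/π) × arcsin(0.5) = 0.333
- 1.96/√0.667 = 2.40
- size = 2 × [1 − Φ(2.40)] = 0.016

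Simulation with n = 81 gives 0.016 for chi-square and 0.053 for McNemar.

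**4. Power.** For a shift from 0.50 to 0.35 with the same latent correlation and n = 81, simulation gives 0.48 for chi-square and 0.66 for McNemar.

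**5. Range over other assumptions.** With n = 84, the size columns take a proportion of 0.5 at both visits and the power columns a change from 0.40 to 0.55:

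| φ | Size, chi-square | Size, McNemar | Power, chi-square | Power, McNemar |
|---|---|---|---|---|
| 0 | 0.055 | 0.050 | 0.51 | 0.49 |
| 0.3 | 0.021 | 0.052 | 0.51 | 0.65 |
| 0.5 | 0.007 | 0.053 | 0.51 | 0.80 |
| 0.7 | 0.0003 | 0.045 | 0.50 | 0.97 |

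In every row with positive correlation chi-square is conservative and loses power.

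**6. Within-arm tests on scores.** Suppose that HAMD falls by 2 points in both arms and the add-ons do nothing. With an SD of 4 and a correlation of 0.5 (both assumed), the SD of change is 4 × √(2 × 0.5) = 4. With n = 81 the noncentrality is 2/(4/√81) = 4.5, and the paired t-test has about 99% power in each arm. Conversely, if each within-arm test had 80% power and the true changes were equal, exactly one arm would be significant with probability 2 × 0.8 × 0.2 = 32%. Neither pattern says anything about the difference between arms.

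**The case against.** The strongest case against has four parts.

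- **No endpoint is hit.** All six outcomes are scores, and no responder rate, remission rate or change of band is defined. The clearly categorical data, such as demographics and adverse events, are ordinarily compared between groups, where chi-square and Fisher are suitable. This stands, and it limits the point to derived categories.
- **The error is in the safe direction.** A reader might infer from the wrong test that false positive claims become more likely. The calculation does not support that under the usual positive correlation; the cost is lost power.
- **The paired method for scores is valid.** The signed-rank test is correct for before-after data. This stands. Its listing shows only that within-group testing is planned.
- **Efficacy does not visibly rest on within-group tests.** A reader might infer that a significant change in one arm and not in the other would be taken as proof. The article does not say so. The trial is a parallel-group randomised design, the sample size is built on the between-group HAMD difference, and between-group tests are named. A formal ranking of the analyses may also stand in a statistical analysis plan that is not shown.

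What the objection does not remove is the categorical sentence itself. It names tests for independent samples for the within-group case, and no reading other than before-after change is plausible given the three visits.

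**Conclusion.** The concern holds in a limited form. The rule for within-group categorical comparisons is wrong as stated. With an assumed latent correlation of 0.5, its actual size is about 1.6% at nominal 5%, and its power is about 48% against 66% for McNemar for an assumed 50% to 35% shift. Over binary correlations of 0.3 to 0.7 the size runs from 0.021 down to 0.0003. These figures depend on correlations and proportions that the article does not give; the direction depends only on the correlation being positive. The error touches derived categories such as severity bands and no defined primary or secondary outcome.

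The placing of within-group tests in the effectiveness analysis is a risk of misreading and not a demonstrated error. Because both arms receive the same standard care, within-arm change cannot isolate the add-on effect, and the text should say which comparison carries the conclusion.

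**What to change.** Make four changes in the Statistical analysis section:

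1. Limit chi-square and Fisher's exact tests to comparisons between the two groups.
2. For any paired categorical comparison that is kept, name McNemar's test for two categories, or a marginal homogeneity test for more than two ordered bands.
3. State that conclusions on efficacy rest on the between-group difference.
4. Report change within each arm as descriptive, with confidence intervals.

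The cost is wording only. No patients, visits or data are added, and the sample size is unaffected because it already rests on the between-group difference.

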#### Inclusion criteria

(1) participants who meet the aforementioned diagnostic criteria;(2) consciousness, stable vital signs, and ability to understand and follow the instructions. Barthel Index (BI) > 20 (Mahoney and Barthel, 1965), FMA (0–95), Mini-mental State Examination (MMSE) meet the following criteria: illiteracy > 17, primary school level > 20, secondary school level (including technical secondary school) > 22, and college-level (including junior college) > 23 points;(3) 25 ≤ age ≤ 85, regardless of gender;(4) first episode of stroke;(5) depression level as mild or moderate (HAMD scores ≥ 7 and ≤ 24);(6) the course of the disease is limited to 2 weeks to 36 months after the stroke; and(7) participants can understand the study protocol and provide written informed consent.

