#### Patient recruitment

In this RCT, we will recruit hospitalized patients from acupuncture departments, rehabilitation departments, and neurology departments in four trial centers, which are the Third Affiliated Hospital of Zhejiang Chinese Medical University, Hangzhou Hospital of Traditional Chinese Medicine, the Second Hospital of Jinhua, and Zhejiang General Hospital of Armed Police.

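### The between-group tests are chosen by observed normality and no baseline-adjusted model is named, which costs some power and leaves the primary effect measure open until the data are seen

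*Protocol article*

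**What the plan says.** For quantitative outcomes, the Statistical analysis section of the protocol article commits to "either parametric tests (Student's *t*-test) or non-parametric tests" (Mann–Whitney U and Wilcoxon signed-rank are the ones listed), and these "will be used, depending on the normality of the distribution". No covariate, regression model or centre term appears there or elsewhere in the article. Baseline values are to be summarised by group. Data from baseline, week 4 and week 8 are to be analysed, but the section does not say whether the groups are compared on raw scores or on change from baseline. "A two-sided 5% significance level will be adopted", and 95% confidence intervals are promised as far as possible.

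The Sample size calculation section works from the difference in post-intervention HAMD. From a pilot study, the HAMD score "in the standard care group was 16.5 ± 4.51", and "the HAMD score in the integrative medicine group was 14.5 ± 3.40". The target is therefore a mean difference of 2 points, with 84 per group before dropout and 202 in total.

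Table 1 schedules HAMD, SDS, ADL, MoCA, PSQI and FMA at baseline.

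**The concern.** There are two separate costs.

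**Efficiency.** If baseline HAMD predicts week-4 HAMD, an unadjusted comparison leaves that predictable variation in the error term. ANCOVA removes a fraction r² of it, using a measurement the trial already takes.

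**Pre-specification.** The t-test addresses a difference in means. Mann–Whitney addresses a shift in ranks and does not by itself supply the mean difference with its interval. The rule lets the observed distribution choose between them, so the primary test and effect measure are not fixed in advance. If Mann–Whitney is selected for HAMD, the reported test no longer addresses the 2-point mean difference that justified the sample size. HAMD, SDS and ADL, all named as primary, could also end up on different effect measures.

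**Working it through.** **Inputs from the protocol article (Sample size calculation and Table 1).** SDs 3.40 and 4.51; difference 2; two-sided α 0.05; power 90%; 84 per group before dropout; 101 per group enrolled; dropout about 20%.

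**Assumed.** The correlation r between baseline and week-4 HAMD is not in the article. It is varied over 0.2, 0.3, 0.5 and 0.6. Entry is restricted to HAMD 7 to 24, which may lower r, so the lower part of the range deserves weight.

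**Step 1: reproduce the plan's figure.** Variance sum = 3.40² + 4.51² = 11.56 + 20.34 = 31.90. Then n = (1.96 + 1.28)² × 31.90 / 2² = 83.72, rounded up to 84 per group. The stated figure reproduces, and it contains no baseline term.

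**Step 2: completers.** 101 × 0.8 = 80.8 per arm.

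**Step 3: standard error and power.** Unadjusted SE = √(31.90 / n). With ANCOVA, SE = √(31.90 × (1 − r²) / n). Power is from the noncentral t distribution with noncentrality 2 / SE.

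| r (assumed) | Variance removed | SE, n = 80.8 | Power, n = 80.8 | Power, n = 84 |
|---|---|---|---|---|
| unadjusted | 0% | 0.628 | 88.6% | 89.7% |
| 0.2 | 4% | 0.616 | 89.8% | 90.9% |
| 0.3 | 9% | 0.599 | 91.3% | 92.3% |
| 0.5 | 25% | 0.544 | 95.5% | 96.1% |
| 0.6 | 36% | 0.503 | 97.7% | 98.1% |

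The normal approximation that the article uses gives slightly higher values (unadjusted: 88.9% at 80.8 and 90.1% at 84). The gains are about the same.

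**Step 4: does the normality switch harm validity?** A simulation used normal data, the article's SDs, 84 per arm and 4,000 runs at each of r = 0.3, 0.5 and 0.7. It compared the t-test, a rule that switches to Mann–Whitney when a Shapiro–Wilk test rejects normality in either arm, and ANCOVA. Averaged over the three settings, type I error was 5.1% for the t-test, 5.3% for the switch and 5.1% for ANCOVA. Single settings ranged from 4.6% to 6.1%, with the three methods close to each other within each setting. Power under the switch was 89% to 91%, about that of the plain t-test; ANCOVA had 92%, 96% and 99%. Only normal data were simulated, so this says nothing about markedly skewed scores.

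**The case against.** **The plan is valid and self-consistent.** Under randomisation an unadjusted comparison is unbiased, the trial was sized on that comparison, and 84 per group reproduces. This stands. A reader might infer bias or an inflated false-positive rate from the normality rule. The documents do not support that: the rule chooses between named tests, the analysts are to be unaware of group, and the simulation shows no material inflation.

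**Covariate models are commonly left to a fuller document.** That would answer a silent article. This one positively names the tests and the rule for choosing between them, so the point concerns stated text.

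**The size of the gain is not known.** This stands, because r is not given. At r = 0.2 the gain is only 1.2 percentage points. The starting value of 88.6% also reflects the dropout allowance, which leaves 80.8 completers instead of 84 and is a separate matter; the 84-per-arm column removes it.

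**Baseline may still be used.** The text does not write out a separate two-sample test at each visit, the signed-rank test is a paired test, and change scores are not ruled out. So it is too strong to say that the baseline score is thrown away; what can be said is that no baseline-adjusted between-group model is named. Change scores are not an equal substitute. With equal variances at the two visits, their variance factor is 2 − 2r, which exceeds 1 when r is below 0.5. At r = 0.3 with 84 per arm, power would be about 78% (normal approximation).

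**Two further tempting readings do not hold.** First, with an assumed baseline SD of 4, the chance baseline difference between arms has SD 4 × √(2/81) = 0.63, and a reader might set this against the 2-point target as a third of it. Only r times the imbalance reaches the week-4 estimate (0.19 to 0.38 points for r = 0.3 to 0.6), and it is already inside the t-test's standard error. It restates the efficiency gain and adds no bias. Second, recruitment from "neurology departments in four trial centers" and the criterion that "the course of the disease is limited to 2 weeks to 36 months after the stroke" might suggest that centre and time since stroke must be in the model. The article states no stratification by either and gives nothing from which their gain could be computed.

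**Conclusion.** The point holds as one of efficiency and pre-specification, not of validity. The article fixes unadjusted tests chosen by observed normality, names no baseline-adjusted model, and so leaves the choice between a mean difference and a rank comparison open until the data are seen, in a trial sized on a mean difference.

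With 80.8 completers per arm, the gain from ANCOVA is about 1 percentage point of power at r = 0.2, 3 at r = 0.3, 7 at r = 0.5 and 9 at r = 0.6. This rests on the pilot SDs, a true difference of 2 points, 20% dropout and an assumed r. The existence of a gain for a predictive baseline is secure; its size is not. The change should be made because it costs almost nothing, but the trial is not unsound without it.

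**What to change.** In the Statistical analysis section, replace the choice between t-test and rank test with one pre-specified model for each quantitative outcome: ANCOVA on the week-4 score, with treatment and the baseline value of the same scale. Centre may be added as an optional covariate, if declared in advance. Report the adjusted mean difference with its 95% CI. Remove the normality-dependent switch and keep the Mann–Whitney test as a sensitivity analysis only.

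A mixed model over weeks 4 and 8 should not be prescribed for every scale as things stand. Table 1 shows no week-8 assessment of SDS, MoCA or FMA, while the Outcome measures text says all outcomes are measured at week 8, and the two must be reconciled first.

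The cost is a change of wording. The data are already scheduled, the model is available in the planned SPSS, and the sample size need not change.
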